**Figure 1 F1:**
[figure not shown]
Map of India with 20 centres marked.

### Stratified sampling

In each region, we predefined a geographic area as urban or rural based on a multistage sampling technique using data from the 2011 census of India. A census enumeration block that usually consists of 125–150 households with a population of 650–700 is the primary sampling unit for urban areas, while villages are defined in the rural areas. Bigger villages are further divided to ensure that approximately 300 households can be covered. The house-to-house survey will be conducted by approaching each household in consecutive streets in each area. If the household members are not available, a further two visits by the fieldworkers are permitted. In each household, all available members aged 40 years or above, who meet the inclusion criteria, will be invited to participate in the study.

The special category groups include two groups: (a) people working under high stress leading to poor and untimely eating habits (such as policemen, truck and taxi drivers, manual labourers, fishermen, factory staff and professionals in stressful jobs) and those presumed to be at low risks such as certain religious groups and (b) people with poor health seeking behaviour and/or under social stigma (such as tribal, slum population and people with infection like HIV or leprosy). All survey clusters and special groups are independent samples. The total population for the study is the total recruited participants in all the 20 regions, including the special population (figure 1).

### Selection of participants

The inclusion criteria are adults who are ≥40 years of age (special groups may contain adult population of any age), who are local residents of Indian origin and are willing to give informed consent (see online supplemental appendix 1 for sample informed consent form).

10.1136/bmjopen-2020-039657.supp1Supplementary data

Exclusion criteria include vulnerable adults in whom it may not be possible to carry out all the tests; pregnant and breastfeeding women; anyone in the opinion of the fieldworkers deemed too ill to be screened; and those who are currently participating in intervention trials with investigational medicinal products.

### Study procedures

The fieldworkers will be responsible for providing adequate information about the study and obtaining consent from willing participants. A unique patient identification number will be allocated for each participant to ensure anonymity. A detailed case report form containing a structured questionnaire will be answered by all participants in the study (see online supplemental appendix 2 for case report form). The data collected will include age, gender, marital status, socioeconomic status (education, occupation and average monthly income), MDRF-IDRS and IHRS that contain questions on lifestyle (smoking and alcohol habits, diet and physical activity and stress),^6 7^ brief medical and ocular history with any relevant medications and/or surgery, and family history of diabetes and cardiovascular disease. The structured questionnaire will be translated into local languages and administered by trained fieldworkers. Questionnaires will be validated in 200 subjects in 2 study sites at the start of the study and the case report forms and the study database will be refined to ensure generalisability and reproducibility.

10.1136/bmjopen-2020-039657.supp2Supplementary data

Anthropometric measurements will be performed using the same kits supplied to all sites, and local fieldworkers will be trained on regular calibration of the kits. Height (in cm) will be measured using a stadiometer (SECA Model 214, Seca Gmbh Co, Hamburg, Germany). Weight (in kg) will be measured with an electronic weighing scale (SECA Model 807, Seca Gmbh Co, Hamburg, Germany) kept on a firm horizontal flat surface. Body mass index will be auto-calculated. Waist circumference will be measured at the smallest horizontal girth between the costal margins and the iliac crest at the end of expiration using a non-stretchable measuring tape. Hip measurement will be done with the arms relaxed at the sides, at the maximum circumference over the buttocks.

BP will be recorded in sitting position in the right arm to the nearest 1 mm Hg using the electronic OMRON machine (Omron Corporation, Kyoto, Japan). Participants with BP ≥140/90 mm Hg and not on antihypertensive drugs will be advised to contact a physician for further evaluation. A simple finger-prick test will be used to assess capillary RBG using a standard POC testing device (OneTouch Verio Glucometer, LifeScan Inc, USA). All participants with known diabetes or those with capillary RBG ≥160 mg/dL and 50 participants with RBG 110–159 mg/dL in each cluster will receive further tests. These include HbA1c estimation using a POC kit (A1c Now Plus, PTS Diagnostics, USA) and POC lipid estimation (Cardiochek PA analyser, PTS Diagnostics, USA). A POC urine sample (Chemstrip Micral dipstick, Roche Diagnostics, Mannheim) will be tested for the presence or absence of microalbuminuria.

Visual acuity in both eyes will be recorded using a tablet/smartphone-based vision check web-based application (Peek Vision). Non-mydriatic fundus photography of both eyes will be done using a handheld retinal camera (Visuscout 100, Zeiss, Germany). This portable and battery-operated camera with in-built Wi-Fi facilities will allow capture of colour and red-free retinal images covering 40° field of view through pupils as small as 3.5 mm. Two fundus images (one macula-centred and one disc-centred) of each eye will be captured. In case of any media opacities making fundus imaging difficult, the anterior segment image of each eye would be taken. A teleophthalmology system will be set up whereby the images captured by each fieldworker will be uploaded to a cloud-based study specific database and graded at the local clinical centre by an ophthalmologist/optometrist (primary grader), as well as transferred to four central reading centres, where grading will be done by a second ophthalmologist (secondary grader). Discrepancies between primary and secondary grading will result in arbitration by a senior retinal consultant. Any participants with STDR, ungradable images and other incidental findings requiring further evaluation will be informed by the fieldworkers and counselled to attend hospital eyecare service. DR will be classified as per the International Clinical Disease Severity Scale for DR as no DR, mild/moderate/severe non-proliferative DR (NPDR) and proliferative DR (PDR).^23^ Diabetic macular oedema (DMO) will be determined as present or absent. STDR would be defined as the presence of severe NPDR, PDR and/or DMO. Artificial intelligence may be applied to grade these images and if found to be as accurate as human graders, it will be incorporated to the screening model.

The well-established and widely used quality of life questionnaire EQ-5D (Euro Quality of life) will also be administered with additional vision ‘bolt-on’ questions and vision-related quality of life.^24–26^ The study flow is shown in figure 2. In addition, centre administrators at each clinical site will be responsible for contacting, by letter or phone, and tracking follow-up of those participants who need further referral to an eye hospital for treatment for STDR or due to ungradable retinal images.

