### Objectives

Our study has three important objectives. The first objective is to determine the ideal tests that could identify people at risk of diabetes and prediabetes in community screening that can be applied to LMIC. In order to accomplish this, we would evaluate the correlation of RBG levels with POC HbA1c levels and decide on a cut-off value for RBG from HbA1c to diagnose prediabetes. Second, we will evaluate whether initial triaging with NL diabetes risk score followed by either RBG or POC HbA1c only to the identified risk group is more effective than screening everyone for diabetes using either RBG or POC HbA1c. Third, we will develop affordable, easily deliverable and clinically effective model to accurately identify people at risk of complications of diabetes in community screening, especially DR.

Secondary objectives are aimed at guiding future policies on screening of diabetes and its complications. As the study involves a large sample and the setting up of a teleophthalmology model to screen for DR across 20 regions in India, we will be able to report the regional prevalence of DR and the associated risk factors, the inter-grader reliability and the accuracy of using artificial intelligence to grade DR. We will also conduct economic modelling and process evaluation of a holistic model for screening of all complications of diabetes. If sample size permits, we will be able to report on region-specific and diverse population-specific rates of diabetes and complications, visual impairment, quality of life and risk models specific to regions to inform local health authorities.

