### Study setting

This community screening will be conducted across 20 regions in India, each led by a local clinical centre with a trained ophthalmologist responsible for the study at that site (figure 1). Each region will have three clusters stratified into urban, rural and a predefined special category of population such as people with poor access to healthcare, or persons that are presumed to be at high risk or low risk of developing diabetes. The study will involve a door-to-door survey, with questionnaires and POC tests performed by fieldworkers. Each cluster will screen at least 800 consenting individuals aged 40 years or above for a cumulative sample size of a minimum of 48 000 participants. If any cluster or centre does not reach their target recruitment, it will be made up by another cluster or centre with the same stratified population.

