### Statistical considerations

The statistical methods will be developed fully within a statistical analysis plan, to be finalised before database lock. Diagnostic accuracy publications will follow recognised Standards for Reporting Diagnostic accuracy studies guidelines and the observational component will follow the Strengthening the Reporting of Observational Studies in Epidemiology guidelines. Table 1 shows the reference and index tests for diagnostic accuracy aspect of the study.

**Table 1 T1:** Reference and Index tests

Community screening for diabetes	
Reference standard	Index test
1. RBG	POC HbA1c Non-invasive diabetes risk scores
Community screening for prediabetes	
1. POC HbA1c	RBG Non-invasive diabetes risk scores
Community screening for complications of diabetes	
1. Serum lipid profile TC Non-HDL cholesterol LDL cholesterol HDL cholesterol TC:HDL ratio Triglyceride	Risk-based screening tool for complications of diabetes using minimally or non-invasive tests
2. HbA1c or RBG	
3. Microalbuminuria	
4. Retinal photography for retinopathy for all people with diabetes	

HbA1c, glycated haemoglobin; HDL, high density lipoprotein; LDL, low density lipoprotein; POC, point-of-care; RBG, random blood glucose; TC, total cholesterol.

Accuracy will be measured by sensitivity and specificity of tests to detect diabetes, prediabetes and people at risk of complications of diabetes. Clustering will be used to accommodate any over dispersion. Consistency of these statistics will be explored across centres and clusters (urban, rural and special population). Area under receiver operating characteristic (ROC) curve will be used to compare models representing the overall performance of tests under comparison. Refinement of test components (eg, combinations of tests or questionnaire items) will be developed, and internally validated where sufficient data are available. The number of false positives will be identified directly from the data. From the estimates of sensitivity and the specificity of diabetes risk score to detect prediabetic (or diabetic) and its estimated prevalence, it will be possible to estimate the false positive rate and the complement of the positive predictive value. All estimates will be accompanied by estimated 95% CIs, which account for both clustering and stratification.

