### Health economics analysis plan

The health economics modelling will address the following three questions: (1) What is the cost-effectiveness of a new screening pathway for diabetes and prediabetes? The screening approaches will comprise: diabetes risk score followed by definitive laboratory tests; diagnostic model which the statistical modelling finds to be more accurate than diabetes risk score followed by definitive laboratory tests; RBG for all without diabetes risk score based prescreen; HbA1c test with no prescreen and; no screening; (2) What is the cost effectiveness of a new screening pathway for DR among people with diabetes? The screening approaches will comprise a new method, which the statistical modelling finds to be accurate; retinal photographs only and no screening and (3) What is the cost effectiveness of a new screening pathway for a range of other complications of diabetes among people with diabetes? The screening approaches will comprise a new method, which the statistical modelling finds to be accurate; a combination of HbA1c, lipids and urine tests and colour retinal images; and no screening. In each case, therefore, one comparator will be a ‘gold standard’ (HbA1c test, retinal photographs and combination of tests as above) and another will be no screening and no treatment until symptoms of DR, DKD or other complications of diabetes are experienced.

The modelling will draw on the following data sources: (1) the data collected through the house-to-house screening and associated retinal images, blood and urine tests on the rates of true and false positives and negatives, the characteristics of people with diabetes and its complications, and their quality of life; (2) the data collected through the study on the cost per person of this screening and its cost per person with diabetes, and the costs of clinic visits and treatments for DR; (3) the data and information from past studies on the incidence rates by age and gender of diabetes, DR and other complications of diabetes, transition rates between different stages of the disease and disease-specific mortality rates; and (4) the data from past studies on the costs of care for people with varying severities of DR and other complications of diabetes and on their quality of life. For those variables on which data cannot be collected in this study or obtained from past studies, expert views will be sought, and sensitivity analyses conducted.

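### Among people without known diabetes, HbA1c is measured according to RBG and never below 110 mg/dL, so HbA1c-referenced results cannot be estimated for the screened population

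*Protocol article*

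**What the plan says.** Study procedures sets who has the further tests. Besides everyone with known diabetes, those with "capillary RBG ≥160 mg/dL and 50 participants with RBG 110–159 mg/dL in each cluster will receive further tests". POC HbA1c is one of those tests. The article gives no rule for testing people without known diabetes whose RBG is below 110 mg/dL, and it does not say how the 50 are chosen.

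HbA1c then serves as the standard in several places:

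- The Abstract makes a model for HbA1c-diagnosed diabetes the primary aim.
- Outcomes makes the correlation of RBG with POC HbA1c the primary outcome.
- Objectives derives the RBG cut-off for prediabetes from HbA1c. It also asks whether triage by risk score "is more effective than screening everyone for diabetes using either RBG or POC HbA1c".
- Table 1 names POC HbA1c as the reference for prediabetes, with RBG and risk scores as index tests.
- Statistical considerations states: "Accuracy will be measured by sensitivity and specificity of tests to detect diabetes, prediabetes and people at risk of complications of diabetes".
- The Health economics analysis plan includes a strategy of HbA1c without a prescreen and draws on study data "on the rates of true and false positives and negatives".

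The adjustment stated is that 95% CIs allow for clustering and stratification. Sampling weights, a correction for partial verification and a restriction to RBG ≥110 are not mentioned. Full methods are left to a SAP that is not shown.

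**The concern.** When the chance of receiving the reference test depends on the index test result, the tested people do not represent the screened people. Here that chance is 1 at RBG ≥160, a small fraction at 110–159 and 0 below 110. HbA1c-positive people below 110 are false negatives of any RBG rule with a threshold at or above 110, and the study never sees them. HbA1c-negative people below 110 are true negatives and are not seen either.

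The primary outcome and the promised prediabetes cut-off are at stake, as are RBG and risk-score accuracy against HbA1c, the comparison with HbA1c for everyone, and the error rates passed to the economic model. A clustered CI changes the width of an interval, not where it is centred.

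**Working it through.** **The plan's own figures.** "Each region will have three clusters stratified into urban, rural and a predefined special category of population", and "Each cluster will screen at least 800 consenting individuals aged 40 years or above". So 20 × 3 × 800 = 48,000, as stated. The sample size section expects 4,800 with known diabetes, which is 10%. That leaves 800 × 0.90 = 720 per cluster without known diabetes. Tests at 110–159 number 60 × 50 = 3,000. The article gives no accuracy or precision figure for the RBG-HbA1c analysis, so there is none to reproduce.

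**What follows with no assumption.** Every tested person without known diabetes has RBG ≥110. Among them, the rule RBG ≥110 has sensitivity 100% and specificity 0% by construction, whatever the truth. A cut-off below 110 cannot be examined.

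**Illustration.** Assumed, not from the document: the RBG split and the HbA1c-diabetes prevalence in each band.

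| RBG (mg/dL) | Share | People per cluster | Prevalence | Positive | Negative | Tested |
|---|---|---|---|---|---|---|
| <110 | 45% | 324 | 2% | 6.48 | 317.52 | 0 |
| 110–159 | 45% | 324 | 8% | 25.92 | 298.08 | 50 (4 positive, 46 negative) |
| ≥160 | 10% | 72 | 60% | 43.2 | 28.8 | 72 |

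For the rule RBG ≥160:

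- Truth: sensitivity 43.2/(43.2 + 25.92 + 6.48) = 43.2/75.6 = 57.1%; specificity (317.52 + 298.08)/644.4 = 615.6/644.4 = 95.5%.
- 110–159 band weighted by 324/50: sensitivity 43.2/(43.2 + 25.92) = 62.5%; specificity 298.08/(298.08 + 28.8) = 91.2%.
- No weights: sensitivity 43.2/(43.2 + 4) = 91.5%; specificity 46/(46 + 28.8) = 61.5%.

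**Range.** A second set of assumptions takes the 4,800 expected newly detected cases as the RBG ≥160 group. That leaves 48,000 − 4,800 − 4,800 = 38,400 people below 160, of whom 3,000/38,400 = 7.8% are tested. If 30–60% of them lie at 110–159, that band is tested at 3,000/11,520 = 26% down to 3,000/23,040 = 13%, and 26,880 down to 15,360 people below 110 are never tested. HbA1c-diabetes rates were varied over 50–70% at ≥160, 4–15% at 110–159 and 0.5–3% below 110:

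| RBG ≥160 | True | 110–159 weighted | No weights |
|---|---|---|---|
| Sensitivity | 0.38–0.85 | 0.41–0.88 | 0.84–0.97 |
| Specificity | 0.94–0.96 | 0.80–0.94 | 0.52–0.67 |

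**Prediabetes cut-off and correlation.** These were simulated from a bivariate normal distribution for log RBG and HbA1c, assuming correlation 0.5–0.7, median RBG 112–130 mg/dL and 25% above the prediabetes limit. The cut-off that maximises the Youden index is 118–136 mg/dL in the whole population, 138–140 with weighting and 156–162 without. The correlation of 0.50–0.70 becomes 0.33–0.61 with weighting and 0.38–0.67 without. Weighting does not restore it because the range of RBG is still cut off at 110.

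**The case against.** The strongest reply is that the article nowhere states an unweighted analysis and defers methods to a SAP, where weights could appear. That stands. A reader might infer from the testing rule that 91.5% and 61.5% are what the plan will report. The document does not support this, and those figures are a conditional worst case on assumed inputs. Statistical considerations does say that counts will be read straight from the data, but only of false positives. At a threshold of RBG ≥160 every positive is tested, so that count is sound.

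Two further limits stand. Table 1 makes RBG the reference for diabetes screening; risk scores judged against it use data collected on everyone and are not affected. Known diabetes is tested at any RBG, so the gap below 110 concerns only people without known diabetes. They are the screening target, however, and pooling in known cases does not fill the gap. The plan to explore already-identified and newly identified diabetes goes some way towards separating the groups.

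It can also be said that with weighting the remaining error is only a few points. That is true of the base case but not always. Take rates of 50%, 4% and 3% from the top band down, with 30% of those below 160 lying at 110–159. True sensitivity is then 2,400/(2,400 + 460.8 + 806.4) = 65%, against a weighted 2,400/(2,400 + 460.8) = 84%. For the economic model, past studies, expert views and sensitivity analyses can fill gaps. That softens the effect there but does not produce study data below 110.

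**Conclusion.** The point holds as a design limitation fixed in the protocol. Weighting can repair the 110–159 band if the 50 are a random sample with a recorded denominator. No analysis can weight a stratum tested with probability zero. As written, the HbA1c-referenced results describe at best people without known diabetes with RBG ≥110, while the objectives speak of the screened population.

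In the base case the unavoidable error is 62.5% against 57.1% for sensitivity and 91.2% against 95.5% for specificity. It grows to 91.5% and 61.5% if no weights are used. These sizes rest on assumed RBG and HbA1c distributions and carry no more certainty than that. In all scenarios tried the direction was the same: sensitivity too high, specificity too low and, in the simulation, the prediabetes cut-off too high.

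**What to change.** 1. Draw the 50 per cluster at random from those eligible, and record the number eligible in each RBG stratum. Weight every HbA1c-referenced estimate by the inverse of the sampling fraction, and analyse people without known diabetes separately. The weighting is SAP wording only. The random draw and the denominators must be settled during fieldwork, because a SAP finalised just before database lock would come too late for them.
2. Keep 50 tests per cluster but move some to a random sample with RBG <110. With 15 per cluster this is 60 × 15 = 900 tests below 110 and 60 × 35 = 2,100 instead of 3,000 at 110–159. No extra tests are needed. The price is lower precision at 110–159 and larger weights: in the base case 324/35 = 9.3 instead of 324/50 = 6.5 in that band, and 324/15 = 21.6 below 110.
3. If step 2 is not adopted, state that the HbA1c-referenced correlation, cut-off and accuracy apply only to RBG ≥110 among people without known diabetes, and drop the study-based claim about HbA1c for everyone. This costs only wording but narrows what the study can conclude.

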**Figure 2 F2:**
[figure not shown]
Study flow diagram.

### Quality assurance

Training of research personnel on study assessments will be done at study initiation meetings, where the core study team, laboratory staff and camera manufacturers will certify individual fieldworkers. In addition, the data manager in the UK will provide on-site training at each centre, as well as continuous remote training throughout the study. The ophthalmologists or their representatives at each clinical centre will be responsible for training their team who may not meet the pre-set criteria or any new member joining the team. A monitoring plan will be in place to ensure that regular remote monitoring is done throughout the study period.

